## Abstract

**Background:**

In frail elderly, the effects of depression and anxiety are deep encroaching. Indicated prevention studies, aimed at subjects with subthreshold disorder, have shown that well designed interventions are capable of reducing the incidence of depression and anxiety. In this randomised prevention trial for elderly, living in the community and suffering from subthreshold depression and anxiety, a stepped care programme was put together to be tested versus usual (GP) care.

**Methods/design:**

Design: randomised controlled trial.

(*See *figure 1: *organisation chart*) together with two other projects, this project is part of a national consortium that investigates the prevention of anxiety and depressive disorders in later life using a stepped care programme. The three projects have their own particular focus. This project is aimed at elderly living in the community.

Inclusion: subjects with a high risk for depression and anxiety without clinical evidence of these syndromes. The participants are 75 years of age and over and have subthreshold symptoms of depression and or anxiety: they score above the cut-off point on the self-report Centre for Epidemiologic Studies Depression (CES-D) scale, but the criteria for a major depressive disorder or anxiety disorder (panic disorder, agoraphobia, social phobia, generalized anxiety disorder) according to a validated interview, the Mini International Neuropsychiatric Interview (MINI) are not fulfilled.

Outcomes:

primary outcome: incidence of a depressive or anxiety disorder over a period of two years (MINI);

secondary outcome: a positive influence of the intervention, a stepped care programme, on symptoms of depression and anxiety and on quality of life as assessed with the CES D, the HADS A and the SF36 respectively (i.e. stabilisation or improvement of symptoms) [see table 1].

Measurements:

Take place at baseline and at 3, 6, 9, 12, 18 and 24 months. Trained independent evaluators assess depression and anxiety status, the primary end point (6, 12, 18, 24 months) [see table 2].

**Discussion:**

Late-life depression and anxiety are characterised by high prevalence, unfavourable prognosis, reduced quality of life, excess mortality and substantial societal costs. No health service, however well equipped, will be able to effectively treat all elderly with depression and anxiety. Therefore, development of (cost) effective means to prevent these disorders is very important.

## Background

Depression and anxiety lead to a serious impairment of daily functioning and quality of life. In frail elderly, the effects of depression and anxiety are especially deep encroaching. Besides a deleterious effect on daily functioning and quality of life, a large number of studies demonstrate excess mortality, disability, handicap and service utilisation [1-7].

The number of elderly is rapidly growing. Almost a third of elderly subjects in the community with subthreshold depression or anxiety will develop a major depressive or anxiety disorder in three years [8]. Therefore, preventing the onset or development of these disorders has a high priority [9,10]. Three types of prevention can be distinguished; universal prevention (aimed at the general population regardless of risk status), selective prevention (aimed at high-risk groups), and indicated prevention (aimed at subjects who have early symptoms of a disorder but do not meet diagnostic criteria). The aims of these types of preventive intervention are reduction of occurrence of new cases and the delay of onset of illness. Additionally, the aims of indicated preventive interventions might be to shorten the duration of the persistence of the early symptoms and to stop the progression of severity so that the subject does not meet DSM IV diagnostic levels [11]. Indicated prevention studies have shown that well designed interventions are capable of reducing the incidence of depression and anxiety [12]. Moreover, they are likely to be more cost-effective than alternative approaches [13]. So, favourable prevention should be well designed and should be aimed at selected groups of elderly, at high risk of developing anxiety or depression. Selected risk factors for the onset of late life depression are [10]: loss of a partner, chronic illness, neuroticism, family history, lack of social support and subthreshold anxiety or depression disorders.

This project aims at the latter; the design and testing of a stepped care intervention to prevent the onset of full blown anxiety and depressive disorder among elderly people with subthreshold anxiety or depression disorder.

The chosen intervention is a stepped care programme [14-16]. In an environment of limited resources, it makes sense to provide expertise, and all the time and individual attention a patient needs, but not more. Stepped care models represent endeavours to maximize the effectiveness and efficiency of decisions about allocation of resources in therapy. Not all elderly with subthreshold anxiety or depression need the same type and intensity of preventive intervention. Frequently, complaints will disappear without active intervention. Some may be helped by reading a self-help book or watching an instructional video. Others could benefit from a brief psycho-educational group conducted by a paraprofessional or problem solving treatment, and still others may require a form of pharmacotherapy or more intensive individual psychological treatment. Although stepped care seems a logical approach from the clinical perspective, surprisingly few studies have actually examined the effects of stepped care programmes.

The proposed generic stepped care programme is based on the following four assumptions: (a) empowerment; participants with subthreshold anxiety and depression need personalised, repeated education, counselling and confrontation with their symptom levels to be able to acknowledge them, (b) different persons require different levels of preventive activities; (c) determining the right level of preventive intervention is critically dependent on proactively monitoring outcome; and (d) stepping up from lower, less intensive to higher, more intensive levels of preventive activities based on monitored outcomes may increase effectiveness and lower costs overall.

## Methods/design

### Aim of the study

a) To put together an indicated prevention intervention for participants 75 years of age and over who live in the community and suffer from subthreshold anxiety or depression (but have no evidence of the clinical disorders) for use by home care in collaboration with mental health care, and

b) To evaluate the effects of this programme versus usual general practitioner (GP) care in the prevention of depressive or anxiety disorders.

### Study design

(*See *figure 2: *flow chart*) The study is a prospective randomised two-armed intervention study. Subjects are randomised by an independent statistician and assigned to intervention (stepped care programme) or control group (care as usual).

### Participants

Adult persons, aged 75 years or older, with subthreshold anxiety or depression capable to give informed consent and with sufficient knowledge of the Dutch language are eligible. Subjects meeting criteria for major depression and/or clinical anxiety, subjects with insufficient mastery of the Dutch language and subjects unwilling or unable to give informed consent are excluded. A subject is defined to have subthreshold depression and/or anxiety when he or she scores above the cut-off score of 16 or more on the Centre for Epidemiologic Studies Depression scale (CES-D, a selfrating inventory for depression and/or anxiety), but does not meet criteria for a full-blown depressive or anxiety disorder as assessed with the Mini International Neuropsychiatric Interview (MINI) [17].

### Sample size

Prospective data derived from the Longitudinal Ageing Study Amsterdam (LASA) study show that 27% of elderly subjects in the community with subthreshold depression develop a major depressive disorder within three years [8]. We assume that this percentage is comparable for subthreshold anxiety, and for combined anxiety and depression. The expected incidence rate of DSM-IV depressive or anxiety disorder within two years is estimated conservatively at 35%. Based on previous work in indicated prevention [12,18], we expect the stepped care programme to reduce the incidence rate of major depression and/or anxiety disorder from 35% to 20%. We aim for 110 participants in each arm (α = 0.05 and a power of (1-β) = 0.80). If after final inclusion the total of participants unexpectedly falls short of the required number to reach a power of 0.8 in our calculations, pooling with the two other projects (see organisation chart) will be considered.

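### The 35% two-year control incidence is called conservative, but it exceeds both cited three-year figures with no linking step, so the stated 80% power rests on an unsupported rate

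*Protocol article*

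**What the plan says.** The Sample size section of the protocol article starts from cohort data: "27% of elderly subjects in the community with subthreshold depression develop a major depressive disorder within three years". It extends the figure: "We assume that this percentage is comparable for subthreshold anxiety, and for combined anxiety and depression". The planning value follows at once: "The expected incidence rate of DSM-IV depressive or anxiety disorder within two years is estimated conservatively at 35" per cent. The programme is then expected to "reduce the incidence rate of major depression and/or anxiety disorder from 35% to 20" per cent, and the size is fixed: "We aim for 110 participants in each arm (α = 0.05 and a power of (1-β) = 0.80"). Neither the sidedness of the test nor a dropout allowance is given with these numbers.

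The Background cites the same reference for a wider population and outcome: "Almost a third of elderly subjects in the community with subthreshold depression or anxiety will develop a major depressive or anxiety disorder in three years".

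**The concern.** Between the cited figure and the planning figure the window shortens from three years to two, yet the rate rises from 27% to 35%. No step connects them. The Background's composite figure, also over three years, is below 35% as well.

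The word conservatively makes this worse. If the programme's relative effect is what carries over, a higher control rate means more events and more power, so a cautious planner would choose a low rate. The event rate and the assumed effect together size the primary comparison. If incidence is nearer to the cited data, the trial has much less chance of detecting the relative reduction it plans on, and a null result could be misread as evidence that the programme does not work.

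**Working it through.** **Inputs.** From Sample size: 27% in three years; 35% against 20% in two years; 110 per arm; alpha 0.05; power 0.80. From Background: almost a third in three years, taken here as 30% to 33.3% (an assumption). Allocation is 1:1, inferred from equal arms.

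**Formula.** Pooled-variance normal approximation, no continuity correction: power = Φ{[d√n − z√(2p̄(1−p̄))] / √[p₁(1−p₁) + p₂(1−p₂)]}, where d = p₁ − p₂, p̄ is the mean of the two rates, and z = 1.645 (one-sided) or 1.960 (two-sided).

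**Reproducing the plan.** With p₁ = 0.35, p₂ = 0.20, n = 110:
- d√n = 0.15 × 10.488 = 1.573; √(2 × 0.275 × 0.725) = 0.631; √(0.2275 + 0.16) = 0.6225.
- One-sided: (1.573 − 1.645 × 0.631)/0.6225 = 0.859, power 80.5%. The size needed for 80% is 109 per arm, so the stated 110 reproduces.
- Two-sided: power 70.5%, and 138 per arm would be needed, so it does not reproduce.

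**Moving the cited risks to two years.** At constant hazard, p(2) = 1 − [1 − p(3)]^(2/3):
- 27%: 1 − 0.73^(2/3) = 18.9% (linear check: 27% × 2/3 = 18.0%).
- 30%: 21.2%. 33.3%: 23.7%.
- In reverse, 35% in two years implies 1 − 0.65^1.5 = 47.6% in three.
- Ratios: 35/18.9 = 1.85; 35/21.2 = 1.65; 35/23.7 = 1.48.

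**Power at 110 per arm**, keeping the planned relative risk 0.20/0.35 = 0.571:

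| Two-year control incidence | Origin | One-sided | Two-sided |
|---|---|---|---|
| 18.9% | 27% in three years | 52% | 39% |
| 21.2% | 30% in three years | 56% | 44% |
| 23.7% | one third in three years | 61.5% | 49% |
| 27% | whole three-year risk within two years | 68% | 56% |
| 35% | planning value | 80.5% | 70.5% |

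Each column should be read only against its own last row. The gap between 80.5% and 70.5% is sidedness, which is a separate point.

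**Alternative effect scale.** Holding the planned hazard ratio, ln 0.80 / ln 0.65 = 0.518, takes 18.9% to 10.3%; power is 57% one-sided and 44% two-sided.

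**Size for 80% power at 18.9%, relative risk 0.571:** 237 per arm one-sided, 301 two-sided.

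**The case against.** The best defence is that 27% is not the rate of the trial's endpoint. It describes major depression arising from subthreshold depression, whereas the primary outcome adds panic disorder, agoraphobia, social phobia and generalised anxiety. The sentence extending the figure to anxiety and to the combination can be read as describing baseline groups, without setting the composite outcome at 27%. Entry also requires two raised CES-D scores at least three months apart (Intervention section, Step 1), which removes early remitters, and recruitment is from a project for frail elderly. Both could raise incidence.

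This stands in part. A reader might infer that the source contradicts 35%. That is too strong: a single-disorder rate cannot contradict a higher composite rate, and the true rate in this population may exceed 19 to 24%. But the article offers neither argument as its reason, and its own composite figure is almost a third over three years. Two fully independent two-year risks of 18.9% give 1 − 0.811² = 34.3%, just under 35%. Even that generous route does not make 35% conservative.

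Nor can one say that 35% strictly requires independence. That depends on constant hazard. If onset were front-loaded, with for example 24% for each disorder by two years (an assumption), 35% would leave 24 + 24 − 35 = 13% with both, against 0.24² = 5.8% under independence.

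The absolute difference of 15 points could be held instead. From 18.9% to 3.9%, two-sided power is 94%. But that is a relative reduction of 15/18.9 = 79%, against the planned 15/35 = 43%, and nothing in the article supports it.

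The fallback of pooling with the two sister projects does not answer the point, because it is tied to a shortfall in participants and not to a low event rate.

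**Conclusion.** The point holds as an unsupported planning assumption described in the wrong direction. The calculation from 35% and 20% to 110 per arm is itself correct on a one-sided reading. The planning rate is about 1.5 to 1.85 times what the cited figures give over two years. Like for like, one-sided power falls from 80.5% to about 52 to 62% at those rates, and to 68% if the whole three-year 27% occurred within two years. Two-sided, it falls from 70.5% to 39 to 49%, and to 56%.

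These figures assume that the relative reduction carries over and, except in the 27% row, that hazard is constant. The linear conversion of 27% gives a slightly lower rate, 18.0%.

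Two stronger readings are not supported. One is that the trial is more likely than not to miss its planned effect: on the reading that reproduces the plan, power stays above one half at 18.9% and above. The other is that the event rate alone takes power from 80% to 39%: about ten points of that drop come from changing the sidedness.

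**What to change.** In the Sample size section:
- Delete the word conservatively.
- Either derive the two-year composite rate from the source, showing the conversion from three years and any allowance for anxiety onsets and for entry on two raised CES-D scores, or state 35% as an optimistic assumption and give its reason.
- Restate power at 110 per arm and relative risk 0.571 for control incidences of about 19%, 24%, 27% and 35%, on one stated sidedness.

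Reconcile the Background and Sample size descriptions of the same reference against the source itself. The article does not show which is right, and they may describe different populations and outcomes, so neither should simply be overwritten with the other.

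The cost is a paragraph and a small table. The stated power becomes less favourable. No added enrolment is required, provided the lower power is acknowledged openly.

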## Discussion

Late-life depression and anxiety are characterised by high prevalence, unfavourable prognosis, reduced quality of life, excess mortality and substantial societal costs [13]. Fortunately, there are hopeful indications that the prevention of new cases of mental disorders seems to be possible [12]. Subthreshold anxiety and depression (i.e., the presence of symptoms of anxiety or depression without evidence of the actual psychiatric disorder) are prognostic variables for major anxiety disorder and depression [13]. Interventions in the subthreshold disorders may prevent the onset of new cases of major depression and anxiety disorder [18]. Demonstration projects of shared care models for indicated prevention of new cases of mental disorders may be an important step forward to reduce the enormous burden of these disorders as was shown by a recent meta-analysis of randomised trials of preventive interventions [12] In this study the indicated prevention of depression and anxiety is attempted by way of a stepped-care programme offering the aged subthreshold depressed or anxious participant, several interventions ranging from noncommittal to the requirement of some engagement.

A preliminary reflection on the limitations and strengths of our design:

A limitation of this pragmatic design is that it will be difficult to weigh the specific contributions of the various elements of this project. Another limitation may be that the quantity and type of questions (questions about mood may be confronting and depressing on their own) can lead to drop-out. The stimulating ideas and activities in the self-help course trying to achieve a positive and active attitude may have an opposite effect since the reader might instead be confronted with his/her limitations.

Strong aspects of this design:

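### The 80% power stated for 110 per arm holds only for a one-sided 5% test, which the article does not declare; at two-sided 0.05 the power is about 70%

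*Protocol article*

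**What the plan says.** All the inputs stand in the Sample size section of the protocol article. The control rate is given as "The expected incidence rate of DSM-IV depressive or anxiety disorder within two years is estimated conservatively at 35" per cent. The effect is an expected reduction: "we expect the stepped care programme to reduce the incidence rate of major depression and/or anxiety disorder from 35% to 20" per cent. The target and error rates follow: "We aim for 110 participants in each arm (α = 0.05 and a power of (1-β) = 0.80"). Under Study design the trial has two randomised arms, and the primary outcome is incidence of disorder at two years on the MINI, so the comparison is of two proportions with equal arms.

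The article does not state the sidedness of α, and the Sample size section names no test, no formula and no allowance for dropout. The same section adds that pooling with the two other consortium projects will be considered if the final total is below the number needed for a power of 0.8.

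One sentence in the Discussion bears on the direction of effect. It says of the ideas and activities in the self-help course that they "may have an opposite effect since the reader might instead be confronted with his/her limitations".

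**The concern.** A bare α = 0.05 in a two-arm trial is normally read as two-sided. On that reading the target of 110 per arm and the power of 0.80 do not fit together for 35% versus 20%.

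Three things depend on this:

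- **Reading of a null result.** A reader would treat a non-significant result as coming from a trial with a 20% type II error. Under a two-sided 0.05 test that error is about 30%.
- **False-positive rate.** If the primary test is instead run one-sided at 5% to match the calculation, the chance of falsely declaring benefit is 5%, not the 2.5% implied by a two-sided 0.05 test. Nothing in the article tells the reader so.
- **The pooling clause.** It is tied to the number required for 0.8 power, and that number depends on the undeclared sidedness.

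**Working it through.** **Inputs (all from Sample size).** p1 = 0.35, p2 = 0.20, difference d = 0.15, n = 110 per arm, α = 0.05, power 0.80. Sidedness is not stated, so both cases are worked.

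**Formula (two proportions, pooled variance under the null, 1:1).**

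n per arm = [z_α √(2p̄(1−p̄)) + z_β √(p1(1−p1) + p2(1−p2))]² / d²

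- p̄ = (0.35 + 0.20)/2 = 0.275
- √(2 × 0.275 × 0.725) = √0.39875 = 0.6315
- √(0.35 × 0.65 + 0.20 × 0.80) = √0.3875 = 0.6225
- z_β = 0.8416 for 80% power
- d² = 0.0225

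**Step 1: reproduce the article's figure (one-sided 5%, z_α = 1.645).**

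- n = (1.645 × 0.6315 + 0.8416 × 0.6225)² / 0.0225 = 1.5626² / 0.0225 = 108.5, so 109 per arm.
- Power at 110: z = (0.15 × √110 − 1.645 × 0.6315) / 0.6225 = (1.5732 − 1.0387) / 0.6225 = 0.859, which gives 80.5%.

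This matches the stated 110 and 0.80.

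**Step 2: the conventional reading (two-sided 5%, z_α = 1.960).**

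- n = (1.960 × 0.6315 + 0.8416 × 0.6225)² / 0.0225 = 1.7616² / 0.0225 = 137.9, so 138 per arm (276 in total).
- Power at 110: z = (1.5732 − 1.2377) / 0.6225 = 0.539, which gives 70.5%.

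**Step 3: does the choice of formula explain the gap?** For the survival rows, the hazard ratio is ln 0.80 / ln 0.65 = 0.518. Expected events at 110 per arm are 110 × (0.35 + 0.20) = 60.5.

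| Method | Two-sided 5%: n per arm | Two-sided 5%: power at 110 | One-sided 5%: n per arm | One-sided 5%: power at 110 |
|---|---|---|---|---|
| Pooled variance | 138 | 70.5% | 109 | 80.5% |
| Unpooled variance | 136 | 71.5% | 107 | 81.1% |
| Arcsine | 137 | 71.0% | 108 | 80.7% |
| Exact enumeration, chi-square test | – | 70.6% | – | 80.7% |
| Continuity-corrected | 151 | 65.0% | 122 | 76.0% |
| Fisher exact | – | 65.5% | – | 76.6% |
| Log-rank, Schoenfeld | about 133 (73 events) | 72.5% | about 105 (58 events) | 81.9% |
| Log-rank, Freedman | about 142 (78 events) | – | about 113 (62 events) | – |

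No two-sided 5% method comes near 110; the lowest is about 133. The standard one-sided formulas without continuity correction lie close to it.

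**Step 4: dropout.** The section states no allowance, so any rate is an assumption. With 10% to 20% loss from 110 per arm, two-sided power would be about 66% to 61%. Dropout therefore widens the gap.

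**Step 5: effect detectable at 110 per arm, two-sided 5%, 80% power.** With the programme arm at 18.4%, p̄ = 0.267 and z = (0.166 × √110 − 1.960 × 0.6256) / 0.6145 = (1.7410 − 1.2262) / 0.6145 = 0.838, a power of 79.9%. The detectable contrast is 35% versus about 18.4%.

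**Step 6: the pooling clause.** The target is 2 × 110 = 220. Under one-sided 5% the number required is 2 × 109 = 218, so full recruitment meets it. Under two-sided 5% it is 2 × 138 = 276, which is 56 more than the target, so the clause would be met even at full recruitment.

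**The case against.** The strongest reply is that nothing has been miscalculated. The article gives α without sidedness, the figure reproduces closely under one-sided 5%, and the hypothesis is worded in one direction: the programme is expected to "reduce the incidence rate of major depression and/or anxiety disorder from 35% to 20" per cent. This stands in part. A reader might infer an arithmetic slip, or that the design simply lacks 80% power. The document supports neither, because under the reading that reproduces 110 the design does have 80% power. But an expected direction is not a declared one-sided test, and nothing else in the article signals one.

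A second reply is that the choice of test belongs in the full protocol or the analysis plan, which are not shown. That is fair for the test itself. It does not remove the point, because the power figure is published here. If a fuller plan specifies two-sided 0.05, the 0.80 is about ten percentage points too high. If it specifies one-sided 0.05, the article leaves its readers unaware of it.

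A third reply concerns the Discussion. A reader might infer that the authors expect the programme as a whole to do harm. They do not say so: the sentence is about the self-help course, which is one component of the programme. It shows only that an adverse effect of that component was considered. Harm is therefore not ruled out, which weakens the case for a one-sided test without settling it.

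**Conclusion.** The concern holds as undeclared sidedness behind a stated power. For 35% versus 20% with 110 per arm, power is 80.5% at one-sided 5% (equivalently two-sided 10%) and 70.5% at two-sided 5%. The type II error on the ordinary reading is about 30%, not 20%, and the shortfall against 138 per arm is 28 per arm. This rests on the article's own rates, equal arms, a simple comparison of proportions and no dropout. Continuity correction, an exact test or dropout lowers the two-sided figure further, and a log-rank calculation raises it only to 72.5%.

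A reader might also infer that the trial must recruit 276. That does not follow: the finding concerns what is claimed for 220, and a trial may go ahead with lower power if it says so.

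**What to change.** Declare in the Sample size section whether the primary test is one-sided or two-sided, and name the formula used.

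- **If two-sided 0.05:** state that 110 per arm gives about 70% power for 35% versus 20%, or that the effect detectable with 80% power is 35% versus about 18.4%.
- **If one-sided:** say so, call it one-sided 5%, and justify it given the authors' own remark about the self-help course.

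Then bring the pooling clause into line. Under two-sided 0.05, simply replacing its threshold with 276 would mean that the clause is met even when recruitment fully succeeds. Either restate the trigger as falling short of the target of 220, or acknowledge that pooling would be considered in any case.

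The cost is a few sentences. No extra participants are needed. The downside is a less favourable power statement or, on the one-sided route, open acceptance of a 5% false-positive rate for benefit.
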